## Abstract

**Background::**

The physical and mental health of college students tends to continuously decline around the world due to lifestyle or behavior habits changes, and pervasive presence of the Internet. Thus it is urgent to improve their health in college life. As a traditional Qigong form is practiced mainly in a standing posture. *Three-Circle Post Standing Qigong* (TCPSQ) is suitable for regular practicing and has beneficial effects on improving the physiological function and psychological emotion by adjusting body, breathing, and mind. The aim of the 3 adjustments is to achieve a state of harmonious unity-integrating these adjustments into “one.” In this study protocol article, we will systematically explore the effectiveness and safety, feasibility of TCPSQ on physical and psychological outcomes of the college students and deeply understand the state of harmonious unity-integrating adjustments of body, breath, and mind into “one.”

**Method/design::**

We will conduct a randomized, assessor, and statistician blinded, parallel-controlled trial comparing the beneficial effect of TCPSQ in college students. A total of 80 eligible college students from the Beijing University of Chinese Medicine (BUCM) will be recruited and randomly allocated into TCPSQ training or unaltered lifestyle control group according 1:1 allocation ratio with allocation concealment. TCPSQ intervention will last 10 weeks. The study period is 18 weeks including a 10-week supervised intervention and a 8-week follow-up. The relevant physical and psychological outcomes, adverse events, and safety will be evaluated at baseline, 6 weeks (at the mid-point of intervention), 11 weeks (at the end of intervention), and 19 weeks (after the 8-week follow-up period) by blinded independent outcome assessors.

**Discussion::**

This is the first randomized controlled trial protocol from the perspective of Qigong connotation to systematically investigate the effect of *TCPSQ* for the physical and mental health of a college student population. If the results in our study prove a significant intervention effect, this would provide preliminary higher-quality evidence and establish an optimal guidance for the application of *TCPSQ* exercise program among a college student population.

**Ethics and dissemination::**

The study was approved by the ethics committee of the Beijing University of Chinese Medicine (approval number: 2018BZHYLL0109). A SPIRIT checklist is available for this protocol. The trial was registered in Chinese Clinical Trial Registry (WHO ICTRP member). Registration number: ChiCTR-BON-17010840.

## Background

1

The World Health Organization (WHO) proposes that^[1]^ health which its definition implies a comprehensive and integrative understanding of people that includes many interrelated social, psychological, and physical factors. Young adults in college life usually involves many rapid changes in the body, mind, and social relationships, the lifestyle, and behaviors that an individual develops during this stage may remain into adulthood and impact future health status.^[2,3]^ With the progress of science and technology, the integration of digital technology within daily life is becoming the cultural norm. More college students spend a majority of their spare time in the digital devices and sedentary lifestyle becomes prevalent among college students globally.^[4]^ Research has shown a substantial decrease in levels of physical activity (PA) among college students during the transition from adolescence into adulthood around the world due to lifestyle or behavior habits changes, and pervasive presence of the Internet.^[5–8]^ It is acknowledged that physical inactivity has been considered to have independent association with the increased risk of weight gain, metabolic syndrome, hypertension, diabetes, heart disease, and even all-cause mortality.^[9–14]^As a result, college students may be a population at increased risk and susceptible to serious chronic diseases later in life.^[15,16]^ Similarly, as a result of risky behaviors and multiple stressors, mental health problems in college students are increasing steeply and becoming a worldwide public health burden.^[17–20]^ Recent national data from the Behavioral Risk Factor Surveillance System (BRFSS) indicate that^[20–23]^ various forms of psychological distresses are more frequently present among college students when compared with their age group in the general population. If left ignored and untreated, mental ill-health issues for the university student population can lead to negative outcomes such as poor academic performance, dropping out or failing out of college, engaging in other risky, dangerous behavior or antisocial behavior, physical illness, and attempting or committing suicide.^[24,25]^ However, It is surprising that only a minority of college students with mental health problems seek and receive adequate help.^[26,27]^ It is therefore urgent to cope with the stressors associated with the college environment and promote both their physical and mental health. Increasing evidences showing the relationship between PA and health have supported the viewpoint that regular exercise or PA has positive effects on physical and psychological health outcomes.^[28–31]^ Recent studies showed that exercise for 8 to 12 weeks was effective for promoting physical fitness and mental health, and improving body composition in college students.^[32–34]^ In addition, PA in adolescents improves brain function and cognitive performance and may help reduce body-mind stress and mood alterations, reductions that can improve academic performance in school.^[35–39]^ As a traditional Chinese mind-body aerobic exercise, Qigong has a thousands of years history and is based on Taoist philosophy and traditional Chinese medicine (TCM) theories.^[40–43]^

Which is a combination of postures relaxation, breathing regulation, meditation, concentration, and gentle movements designed to improve holistic health and to facilitate mind-body integration.^[41–45]^ Specifically, the word “Qigong” involves 2 theories: “Qi,” the vital energy of the body, and “Gong,” the training or cultivation of Qi.^[46,47]^ Qigong challenges the foundations of modern Western biomedical thought, sharing as it does the Eastern philosophy, allows the exerciser to strengthen and gain control over Qi, the life energy that flows in channels (meridians) in the body.^[48–51]^ Qigong exercise can be practiced as a “static” (sitting, lying, or standing) or “dynamic” (moving) style,^[52]^ its aims to achieve a harmonious flow of vital energy (Qi), blood, and fluid throughout the body by long-term practicing to relieve pathological stagnation and regulate the functional activities of meridians and visceral organs through regulated breathing, mindful concentration, and gentle movements.^[41,44,47,50,51,53–61]^ With regular practice and rehearsal of the structured postures or movements, as well as concentration on mind and breath, practitioners can achieve an efficiency of “body relaxation and mind calm” and *Tian Ren He Yi* (the theory that mankind is an integral part of nature) so as to experience mood stabilization and improved strength and fitness.^[53–62]^ Due to its significant promotion of human health and ease of learning, Qigong is appropriate for nearly anyone of any age or physical condition, especially among young people. What is more, it can be practiced any place and any time, without any special equipment.^[46,49,50,61,63,64]^ A growing research suggests that Qigong may promote beneficial changes in the central nervous system (CNS), including favorable changes in dopaminergic and other neurochemical systems as well as effective for hormonal variation in the sympathetic nervous system (SNS) and/or hypothalamic-pituitary-adrenal axis (HPAA), and glucose use in specific regions of the brain associated with mood elevation, memory, and attentional processing, including the hippocampus, prefrontal cortex, and anterior cingulate gyrus.^[41,42,46,51,56,64–74]^

*Post Standing Qigong (PSQ)*, translated as the“*Zhanzhuang Qigong,*” is a traditional Qigong form practiced mainly in a standing posture. It stresses not only body alignment, but also breathing and the mind. The word “*Post*” suggests the root of a tree, which is deep in the earth and unshakable. Though associated with *Martial Arts Qigong (MAQ)*, *PSQ* is also used for health preservation and to treat diseases.^[75]^*PSQ* can enhance Qi function through the whole exercise of body posture, breathing, and meditation to calm the brain, relax the body, and keep balance of physical and psychological; thus emphasizing on the concept of integrity is the feature of *PSQ*,^[75]^ studies reported that the functions of *PSQ* were not development of partial body functions and treatments of certain disease but comprehensive exercise by recuperating body and psychology.^[75–84]^ Simplicity and popularity are the another of feature of *PSQ*. Practitioners exercising *PSQ* do not depend on place, exercise equipment, whatever sex or different age levels^.^^[75]^ Current studies have suggested that *PSQ* training appears to have substantive benefits for adults with some physical and mental disorders such as anxiety, obsessive-compulsive symptoms, depression, insomnia, neurasthenia, angiocardiopathy, hypertension, hyperlipidemia, metabolic disturbance, digestive diseases, spinal problems, kneecap strain, osteoarthrosis, and type 2 diabetes mellitus (T2DM).^[75–84]^ For young adults, particularly the college student population, the results from few studies also indicated that *PSQ* has a potential benefit on reducing depression, stress and anxiety, building self-control, and a healthy mind, and improving attention, cognitive function, body constitution, and physical function.^[75,84–88]^

At the same time, the postures adopted by various schools differ from one another, but representative variations include the *Natural Post, Three-Circle Post, Downward Pressing Post, Rounded Post, Horse Mounting Post, Subduing Tiger Post, Shaolin Sword Finger Post, and so forth.*^[75]^*Three-Circle Post Standing Qigong (TCPSQ)* exercise is one of the common forms of *PSQ*. Standing in relaxed posture, circling the arms akin to hugging a tree trunk or holding a ball, breathing deeply and steadily, mentally focus on the rotating balls or tree trunk with a relaxed attitude, maintaining balance is central to *TCPSQ.* Compared with other *PSQ*, the advantage of *TCPSQ* is its strong symmetry, which is more significant in correcting physical imbalance and body asymmetry caused by unhealthy postures in the daily life. Moreover, it can be learned easily and is less physically and cognitively demanding compared with other *dynamic Qigong*. Which is suitable for regular practicing and has beneficial effects on improving the physiological function and psychological emotion by adjusting body, breathing, and mind.^[75]^ Several studies have indicated the beneficial effects of *TCPSQ* on reducing blood lipids, lowering blood pressure, reducing blood sugar, and glycosylated hemoglobin and have proven the benefits of *TCPSQ* on cardiopulmonary function and body morphology, additionally, significant improvement has been reported in balance, attention, cognitive function, gravitational stability, strength and flexibility, as well as pain reduction and improvement in metabolic capability, bone regeneration, physical fitness, sleep quality, psychological well-being, and immune function.^[75–77,80,83–88]^

However, few studies are randomized control trial (RCT), most have significant methodological limitations, to date, no study of high methodological quality has been conducted to investigate whether *TCPSQ* can be recommended as an effective exercise for improving the emotional state, psychological well-being and physical fitness of young adults, particularly the college student population, well-designed rigorous RCTs related to the effects of *TCPSQ* on psychological and physical well-being of college students are still scarce. In this study protocol article, we will design a RCT to systematically evaluate the effects of *TCPSQ* on physical and psychological outcomes of the college students including bioelectrical activity of cortical neurons, biomechanical balance of spinal column (dynamic and static), morphological balance of spinal column, degree of thoracic breathing and abdominal breathing, electrical activity of the heart, cardiopulmonary function, as well as self-reported symptom intensity, anxiety, depression, personality, self-esteem, quality of sleep, constitution in Chinese medicine, symptoms induced by spinal problems, and self-evaluation of Qigong training.

## Method/design

2

### Study objective and hypotheses

2.1

The primary aim of this RCT will be to systematically evaluate the effectiveness and safety, feasibility of *TCPSQ* on physical and psychological health of college students by observing the difference between the *TCPSQ* group and unaltered lifestyle control group.

The primary hypothesis of this study is that college students who receive a 10-week *TCPSQ* training intervention will show greater improvement in physical and psychological health than those who keep to their usual daily lifestyle, as assessed immediately after the 10-week training intervention, and these benefits will continue until the end of 8-week follow-up.

The secondary aims of this study are:

1.To investigate if *TCPSQ* is more beneficial to biomechanical balance and morphological balance of spinal in college students than usual daily lifestyle.2.To investigate the effect of *TCPSQ* on specific domains of breathing degree and heart activity in college student.3.To explore the mechanism of action of *TCPSQ* on psychological health in college students based on electroencephalogram and psychological self-rating scales.4.To verify whether the gains in both physical and psychological capacities related to balance and mobility and quality of life of college students trained by *TCPSQ.*

We hypothesis that college students with subhealthy state who receive a 10-week *TCPSQ* training intervention will achieve greater improvement in specific domains of spinal balance, breathing degree, heart activity, and show favorable changes in function of related brain regions than those who maintain their usual daily lifestyle.

### Study design

2.2

This study was designed as a pilot 2-arm, randomized, assessor and statistician blinded, parallel-controlled trial comparing the beneficial effect of *TCPSQ* in college students with unaltered lifestyle control repeatedly. A total of 80 eligible college students from the Beijing University of Chinese Medicine (BUCM) will be recruited and randomly allocated to either the *TCPSQ* group or control group (unaltered lifestyle) according to 1:1 allocation ratio with allocation concealment. The participants in the *TCPSQ* group will accept a 10-week *TCPSQ* exercise training, at the same time the others in the control group will maintain their original lifestyle. The study period is 18 weeks including a 10-week supervised intervention and a 8-week follow-up with relevant physical and psychological outcomes will be measured at baseline, 6 weeks (at the mid-point of intervention), 11 weeks (at the end of intervention), and 19 weeks (after the 8-week follow-up period) by the assessors who are not participated in this trial at the Qigong and Human Science Laboratory of BUCM. The statistic analysis will be performed by special statisticians who are not involved in this trial. The flow diagram for this trial is presented in Figure 1.

**Figure 1 F1:**
[figure not shown]
Flow diagram of study design.

### Sample size

2.3

There are no previous clinical trials to explore the beneficial effect of *TCPSQ* on college students from the integrating with physical fitness and psychological well-being. Therefore, this study is designed as a pilot study to calculate the appropriate sample size for future randomized clinical trials. Each group should include 30 participants, which is the minimum sample size for evaluating the effect of *TCPSQ*. Considering a 20% attrition rate, a total of 80 participants are necessary, with 40 participants in each group.

### Participant and recruitment

2.4

A total of 80 college students from BUCM who are in the first or second grade aged 18 to 25 years will be recruited into the study. Recruitment plan of participants will be performed at the campus of BUCM by schoolyard media advertisement, posting up posters, and school radio, sending leaflets and brochures. Those who are interested in taking part will contact the research assistants directly who will determine eligibility according to the inclusion and exclusion criteria at the recruitment office. The research assistants will briefly explain the purpose of the study and ask if they have an interest in participating. If an applicant meets the study criteria, he or she will be required to sign a written informed consent agreement before enrollment in this trial. Participants will also be asked to sign a declaration stating that they will participate fully to the best of their ability and will continue their involvement in the *TCPSQ* program once commenced. A log book will be given to each participant to monitor involvement and practice *TCPSQ* as well as any reporting of adverse events (AEs).

### Inclusion criteria

2.5

Participants meeting the following criteria will be included. They must be:

(1)college students, be a fulltime student at first or second grade, be aged 18 to 25 years;(2)right handed(3)voluntarily participate in this research(4)able to provide the written informed consent form for participation in the trial and take part in *TCPSQ* training on time,(5)truthfully fill out the training record form and cooperate with the physical and psychological outcomes measure.

### Exclusion criteria

2.6

Participants meeting the following criteria will be excluded:

(1)Being or having been engaged in a long-term regular practice of *PSQ* or other forms of *Qigong* or athletic sports;(2)Being a member of the Martial Arts Association, Dance Association, Aerobics Association, Sanda Association, or Taekwondo Association, and so forth;(3)Those who have family history of psychosis, neurasthenia, stress disorder, personality disturbance, mental sickness induced by taking psychoactive substances;(4)Those who have suffered from malignant tumor, severe consumptive disease, cerebrovascular disease, communicable disease, mental illness, and severe cardiovascular, liver, kidney, gastrointestinal and hematological diseases, musculoskeletal system diseases, or other contraindication to mild- to moderate-physical exertion;(5)Those who used antipsychotic drugs or anti-insomnia drugs at a month before the start of the study;(6)Those who with a metal or heart pacemaker implanted in the body;(7)Those who being or having been participated in other clinical trials that affect the physical and psychological outcomes of this study.(8)Those who inability to comprehend and complete the study assessments or comply with the study instructions.

### Withdrawal criteria

2.7

Participants will be withdrawn from the trial if they present any of the following conditions: poor compliance (mean compliance < 85% at the last estimation) or noncompliance, occurrence of a serious adverse event, initiative exits are unable to progress because of sudden disease, members in the control group have regularly engaged in *TCPSQ*, request to be withdrawn from the trial.

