#### Control group

2.11.2

The participants in the control group will not receive any specific training. They will be informed to maintain their original daily lifestyle in the intervention period (based on the initial inclusion criteria that they were not exercising on a regular basis) and requested not to commence any regular exercise regime or participate in other mind-body exercises, such as yoga or other forms of Qigong. On the completion of the study they will be given the same 10 weeks of *TCPSQ* training after the 19 weeks so as to increase involvement compliance rate.

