#### Intervention regimen

2.11.3

*TCPSQ* training consisted of an initial workshop conducted over 3 consecutive half-days by 2 qualified coaches. Participants received concentrated training: this consisted of instruction in source of *PSQ*, understanding in the essence and beneficial effects of *PSQ*. Participants will be taught the relevant knowledge of *TCPSQ*, which includes the rationale that *TCPSQ* constitutes a health benefit, the action essence of *TCPSQ* the philosophy opinion of *TCPSQ*. The instruction of *TCPSQ* will be both verbal and visual. And participants will be also obtained information about procedure of this study, and the matter needing attention of individuals in the trial. Participants will be required to learn the key movements known as “regulating body, breathe, mind” and ancillary exercises with multiple repetitions of *TCPSQ* until they master it, as will be confirmed by the professional coaches. The coaches will visit each individual daily to ensure that the movements are being correctly practiced.

Once initial concentrated training was complete, participants were asked to practice supervised training. Participants of *TCPSQ* group will undergo the regular training together for the last 10 weeks at a frequency of 5 days per week (from Monday to Friday), training will be performed for 50 minutes per day, each session will include a warm-up for 10 minutes. Specified *TCPSQ* performed and refined for 30 minutes, the practice method successively as follows: body adjustment; breathing adjustment; mind adjustment, and cooling down for 10 minutes. The instructors will visit each individual to ensure that the movements are being correctly practiced. All participants will be required to fill self-made *TCPSQ* training self-evaluation scale (including self-evaluation of training difficulty, the relaxation or tensity or pain and fatigue of various parts of body, perspiration level, saliva secretion level, body sense of warmth, breathing control state, meditative state of mind, abnormal physical and mental reaction, level of coordination between body and mind during and after training) and record their daily PA information during the intervention period. The compliance of the subjects will be assessed in terms of the number of training attended and the number of training self-evaluation scale per day.

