### Statistical analysis

2.16

Collected data will be recorded on standardized forms. Descriptive statistics will be calculated for dependent and independent variables. This analysis will include summary statistics of demographic information and outcome measures. Continuous variables will be summarized as mean (SD) ± standard deviation for normal distribution, and median (IQR) ± interquartile range for non-normal distribution. Normality will be tested using *Kolmogorov–Smirnov* test and categorical variables will be presented with frequencies or percentages. Appropriate transformations will be applied in cases of non-normal distribution. For the variables with a normal distribution, differences in terms of outcomes between groups will be compared using an independent *T-*test. If the variables have a non-normal distribution of ordinal level, statistical comparison between groups will be made by using the *Mann– Whitney U* test even after suitable transformations. Measures with a discrete distribution will be expressed as percentages and analyzed by the *X*^*2*^ or Fisher's exact test as appropriate. Subgroup analysis will be performed according to participants’ gender, personality, and constitution of TCM. Analysis of variance (ANOVA) will be used for the repeated measurement data, and *post-hoc* comparison between groups at different assessment time points will be conducted using multiple comparisons with adjustment to the type 1 error rate. Analysis of the primary and secondary outcomes will be on the basis of intention-to-treat (ITT) population and per-protocol (PP) population. The result of the ITT analysis will be compared with that of the PP analysis to check whether the results are consistent or not. If the statistical results of the ITT and PP population data are the same, the results will be deemed to be reliable; if they are contrary, we intend to adopt the results of the ITT population. The method of processing missing data will be the last observation carried forward (LOCF). This refers to assigning the last observed value of the end point indicator to the subsequent missing evaluation point; that is, the last observation response will be considered to be the study end point. Safety will be evaluated by tabulations of AEs, and will be presented with descriptive statistics for each group. A chi-square test or a Fisher's exact test will be used to compare the frequency difference in AEs between the 2 groups, and severe AEs will be listed in detail. To explore potential factors which might influence adherence, a logistic regression model and a linear mixed-effects model will be used and adjusted for potential confounders. Adherence-related data will be taken from training log records. All statistical tests will be implemented using IBM SPSS 21.0 with bilateral inspection. The level of statistical significance is assumed at 2-sided *P* value <.05.

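### Section 2.7 withdraws randomised participants from the trial for low compliance or control-arm practice of TCPSQ, so the prevailing ITT result rests on carried-forward values where the protocol itself stopped follow-up

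*Protocol article*

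**What the plan says.** Section 2.7 opens "Participants will be withdrawn from the trial if they present any of the following conditions" and lists, among others, "poor compliance (mean compliance < 85% at the last estimation) or noncompliance" and the case where "members in the control group have regularly engaged in" TCPSQ. A participant's own request to leave is a separate entry in that list, so the other entries can fall on people who are willing to continue.

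Section 2.11.3 gives the measure: "The compliance of the subjects will be assessed in terms of the number of training attended and the number of training self-evaluation scale". On the other arm, section 2.11.2 says "The participants in the control group will not receive any specific training"; controls are given the programme only after week 19.

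Section 2.9 says that data gathered before a withdrawal are retained and analysed. Section 2.16 says "Analysis of the primary and secondary outcomes will be on the basis of intention-to-treat (ITT) population and per-protocol (PP) population". It fills missing assessments by LOCF, treats agreement between the two analyses as a sign of reliability, and adopts the ITT result if they conflict.

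**The concern.** Poor adherence and contamination are the deviations that an ITT analysis is meant to keep, with outcomes observed after they occur. Section 2.7 instead makes them reasons to end trial participation. The two criteria act on different post-randomisation behaviours in the two arms, so the lost follow-up need not balance.

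Three things are at stake:
- The week-11 comparison, which tests the primary hypothesis (2.1), and the week-19 self-reported scales would contain imputed values for participants who could have been measured.
- The ITT/PP comparison loses force, because the ITT side holds no observed outcomes after withdrawal for the people who separate the two sets.
- Feasibility is part of the primary aim, and 2.16 plans to model adherence from training logs. Those logs would stop early for the least adherent.

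**Working it through.** **Inputs from the protocol article.** 30 per group, 20% attrition, 40 per group randomised (2.3); 5 sessions a week for 10 weeks (2.11.3); the 85% threshold (2.7); LOCF, ITT priority, two-sided 0.05 (2.16). **Assumed, because the document gives no figure:** the attendance distribution, the share withdrawn, the correlation of compliance with outcome, any improvement common to both arms, and how far week-6 values have moved towards week 11.

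1. **The plan's own figure.** 30/(1 - 0.20) = 37.5, so 38 per group; the plan has 40, which is on the safe side. The attrition allowance is 0.20 x 40 = 8 per group. The point does not depend on this figure.

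2. **Who can fail the threshold.** Compliance counts sessions attended and training forms completed (2.11.3), and controls have no sessions (2.11.2). The 85% threshold as measured therefore applies only to the TCPSQ arm. The contamination criterion applies only to controls.

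3. **Reach.** 5 x 10 = 50 sessions and 0.85 x 50 = 42.5. Attending 43 passes (86%) and attending 42 fails (84%), so missing 8 triggers the rule. This takes attendance alone as the measure and all 50 sessions as the denominator. The probability of attending at most 42 of 50 was computed by a binomial distribution (all students alike) and by beta-binomial distributions with concentration 5, 10 and 20 (students differ):
   - mean attendance 95%: 0.3% to 11%, about 0 to 4 of 40;
   - mean attendance 90%: 12% to 24%, about 5 to 10 of 40;
   - mean attendance 85%: 38% to 48%, about 15 to 19 of 40.

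   At 90% attendance the rule alone could use up the allowance of 8.

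4. **What is carried forward.** Withdrawal before week 6 leaves only baseline, so week 11 is entered as no change. Withdrawal between weeks 6 and 11 carries the week-6 value. Withdrawal after week 11 costs only the week-19 scales.

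5. **Bias at week 11 when there is no true effect.** Simulation with 40 per arm and 10,000 runs. The outcome is in SD units, higher is better, and positive bias favours TCPSQ. The least compliant 20% of the TCPSQ arm and no controls are withdrawn; the correlation r of compliance with outcome is 0, 0.3 or 0.5; the common drift is 0 or 0.5 SD.
   - everyone still measured: bias about 0, type I error about 5%;
   - week-6 value carried forward: -0.05 to +0.06 SD, type I error 5% to 6%;
   - baseline carried forward: -0.10 to +0.13 SD, type I error 5% to 10%;
   - for contrast, withdrawn participants dropped from the analysis: 0 to +0.17 SD, type I error 5% to 11%.

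   With 30% withdrawn, carrying forward (week 6 or baseline) gives -0.15 to +0.17 SD and type I error up to 14%.

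6. **Hand check.** The lowest fifth of a standard normal lies on average 0.280/0.20 = 1.40 SD below the mean. The bias is then about 0.20 x k x (1.40 r - drift), with k = 1 for baseline and k = 0.5 for week 6, which the simulation places halfway.
   - r = 0.5, drift 0: 0.20 x 0.70 = +0.14 (baseline) and +0.07 (week 6); simulated +0.134 and +0.064.
   - r = 0, drift 0.5: 0.20 x (-0.5) = -0.10 and -0.05; simulated -0.095 and -0.045.

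   The sign depends on whether the lower outcome of poor compliers outweighs the improvement that carrying forward discards.

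7. **Scale.** The standard error of the arm difference with 40 per arm is sqrt(2/40) = 0.22 SD.

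**The case against.** The strongest reply is that the plan already protects the randomised comparison. Section 2.9 keeps the data, 2.16 fills gaps by LOCF and lets ITT prevail, and nothing says that a withdrawn participant leaves the ITT set. All 80 can be analysed as randomised. The simulated bias under LOCF at 20% withdrawn is below one standard error, and this is a declared pilot. That reply stands against several stronger readings:

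- **That ITT stops being a comparison of randomised groups.** This would be so only if the ITT set left these participants out. The article does not say that, and the exact definition of the set may sit in an SAP that is not shown.
- **That the bias favours TCPSQ.** That follows from dropping poor compliers. Under the planned LOCF either sign is possible.
- **That weeks 6, 11 and 19 are all lost.** Section 2.7 does not date the last compliance estimation. If it falls at the end of training, weeks 6 and 11 may already be measured.
- **That the whole compliance clause reaches only the TCPSQ arm.** The threshold does, but noncompliance as a separate ground has no stated measure and could reach controls, who also keep activity diaries (2.11.3).
- **That the ITT/PP check or the adherence model becomes worthless.** Carried-forward ITT still differs from PP, and logs up to withdrawal remain. Both are weakened.

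The reply does not remove the conflict itself. Section 2.7 ends follow-up for the deviations that ITT should observe, and no later analysis plan can recover outcomes that were not collected.

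**Conclusion.** The point holds in a limited form. Section 2.7 stops follow-up on post-randomisation behaviour that differs by arm. The ITT result therefore depends on LOCF values for participants whose assessments the protocol itself ended. With an assumed 20% of the TCPSQ arm withdrawn, the null bias is roughly -0.05 to +0.06 SD or -0.10 to +0.13 SD, depending on whether week 6 or baseline is carried forward. It grows with the share withdrawn. These figures rest on the assumed correlation, drift and week-6 values, and on attendance over 50 sessions being the compliance measure. The bias is modest and its direction cannot be foretold, but it is avoidable: measuring everyone brings it to about 0.

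**What to change.** State in 2.7 that participants who meet the compliance or contamination criterion stay in the trial, are invited to all remaining planned assessments, and are analysed in ITT as randomised with their observed outcomes. Use those two criteria only to define the PP set; the 85% figure need not change. Reconcile 2.7, 2.9 and 2.16 accordingly, and make clear that 2.9 also covers withdrawal imposed by the protocol.

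This change does not touch the serious-adverse-event and sudden-disease conditions. However, 2.7 lists a serious adverse event as a condition for withdrawal, while 2.14 leaves withdrawal after such an event to a decision. Those two sections must be reconciled by the investigators.

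The cost is a short amendment and a few more participants at assessments already planned. Some will decline, so some missing data will remain.
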